## Abstract

**Background:**

Gastric cancer is the fourth most common malignant disease worldwide, with lower one-third gastric cancer the most common type. Distal gastrectomy with D2 lymph node dissection was recommended as a standard surgery for distal gastric cancer patients. However, some controversy remains about the anastomosis of the residual stomach and the intestine. The objectives of this trial are to test the hypothesis that uncut Roux-en-Y anastomosis can reduce postoperative complications and improve nutritional status more effectively than Billroth II anastomosis in gastric cancer patients after D2 gastrectomy.

**Methods/design:**

This multi-center, prospective, phase III, randomized controlled trial will compare the efficacy of uncut Roux-en-Y anastomosis versus Billroth II anastomosis in phase I–III patients with initial treatment of radical distal gastrectomy. Patients will be randomized to undergo either the intervention (uncut Roux-en-Y anastomosis) or the control (Billroth II anastomosis). We will recruit 832 patients who meet the trial eligibility criteria and will follow the patients after surgery to observe postoperative complications and nutrition status for 5 years. The primary assessment indices of the study are reflux gastritis, esophagitis, bile regurgitation, and anastomotic ulcer. The secondary assessment indices are nutritional status, quality of life, perioperative complications, overall survival rate, and others. When the number of cases reaches 400, an interim analysis will be performed to identify any evidence of definite superiority of the experimental intervention.

**Discussion:**

We aim to test the hypothesis that uncut Roux-en-Y anastomosis can reduce postoperative complications and improve nutritional status more than Billroth II anastomosis in gastric cancer patients after D2 gastrectomy. The results of the trial will contribute to the best evidence on which to base the reconstruction of distal gastrectomy.

**Trial registration:**

Chinese Southern Gastric Cancer Conference CSGC002 Trial. ClinicalTrials.gov, NCT02763878. Registered on 5 May 2016.

**Electronic supplementary material:**

The online version of this article (10.1186/s13063-019-3531-0) contains supplementary material, which is available to authorized users.

## Background

Gastric cancer remains the fourth most common malignant disease and is the second leading cause of cancer-related deaths worldwide, although the mortality is decreasing in many countries, such as in North America and Eastern Europe [1, 2]. Lower one-third gastric cancer is the most common type of gastric cancer, accounting for more than 50% of cases [3]. For these patients, distal gastrectomy with D2 lymph node dissection was recommended as the standard surgery [4].

To date, we have three main techniques for anastomosis between the residual stomach and the intestine—Billroth I anastomosis, Billroth II anastomosis, and Roux-en-Y anastomosis—among which Billroth II and Roux-en-Y anastomosis have been the most used [5–7]. However, some controversy remains regarding anastomosis of the residual stomach and the intestine, as each anastomosis has its own advantages and disadvantages [8–10]. Billroth I anastomosis is simple for surgeons to perform, but the procedure can only be performed on specific patients as it is likely to cause high tension for the anastomosis and reflux diseases, including reflux gastritis and esophagitis [11, 12]. Billroth II anastomosis is also simple to perform and is associated with lower anastomotic tension, but it is possible to cause bile reflux gastritis, esophagitis, or dumping syndrome [13]. Roux-en-Y anastomosis has been explored for use in distal gastrectomy for the past 20 years. It can partly resolve the reflux diseases that always occur after Billroth I and Billroth II anastomosis [14, 15]. However, Roux-en-Y anastomosis is more complex than the other two kinds of anastomosis; in this procedure, the small intestine is cut off to connect the residual stomach with the proximal jejunum, interrupting the continuity of the small intestine and influencing nerve impulse transmission [16, 17]. In theory, an ideal gastrointestinal reconstruction after distal gastrectomy would have the following characteristics: continuity of the digestive tract, less occurrence of postoperative syndromes, and easy acceptance by surgeons.

Uncut Roux-en-Y anastomosis was first reported by Van Stiegmann and Goff in 1988 [18]. In 2005, Uyama et al. [19] first reported laparoscopy-assisted uncut Roux-en-Y reconstruction after distal gastrectomy. The anastomosis method of the uncut Roux-en-Y is shown in Fig. 1. In theory, this anastomosis has an anti-reflux function and can eliminate the occurrence of Roux stasis syndrome [20, 21]. Moreover, this anastomosis preserves the continuity of the gastrointestinal tract, maintains nerve impulses generated from the normal pacemaker of duodenum to distal jejunum, and prevents ectopic pacemakers [22, 23]. Kim et al. first reported that uncut Roux-en-Y anastomosis could help to reduce the occurrence of reflux gastritis and bile reflux [24]. In the retrospective study of Liang and colleagues [25], comparing the procedure with Billroth II anastomosis, the occurrence of anastomotic ulcer and reflux gastritis after gastrectomy was lower with uncut Roux-en-Y anastomosis. Thus, the uncut Roux-en-Y is controversial but promising. However, there have been few reports on this anastomosis, most of which were either retrospective studies or had small sample sizes. No studies of postoperative nutritional status have been reported for gastric cancer patients after D2 gastrectomy with uncut Roux-en-Y anastomosis. We propose to develop this multi-site, prospective clinical trial to investigate the advantages of uncut Roux-en-Y anastomosis compared with Billroth II anastomosis.

**Fig. 1 Fig1:**
[figure not shown]
The general view of surgical procedures. The left one is Uncut Roux-en-Y anastomosis, while the right one is Billroth II annastomosis

### Trial objectives

The objectives of this trial are as follows:To test the hypothesis that uncut Roux-en-Y anastomosis can reduce postoperative complications and improve nutritional status for gastric cancer patients after D2 gastrectomy compared to Billroth II anastomosisTo provide class-one evidence for the reconstruction of distal gastrectomy

## Methods/design

### Trial design

This is a multi-center, prospective, phase III, randomized controlled trial, supported by the China Southern Gastric Cancer Cooperation (CSGC). The Sixth Affiliated Hospital of Sun Yat-sen University associated with the other eighteen hospitals in Southern China is responsible for this trial. Patients from the coordinating centers who satisfy the pre-specified criteria will be included and randomly divided into two groups: an experimental group undergoing uncut Roux-en-Y anastomosis and a control group undergoing Billroth II anastomosis. We will follow the patients after surgery to observe postoperative complications and nutrition status for 5 years. The study flow chart is shown in Fig. 2. An interim analysis will be undertaken when 400 eligible cases are enrolled, and we will subsequently evaluate whether the trial should be continued or terminated depending upon the results of the interim analysis. The example template of recommended content for the schedule of enrolment, interventions and assessments is shown in Fig. 3.

**Fig. 2 Fig2:**
[figure not shown]
Flow chart of the study

**Fig. 3 Fig3:**
[figure not shown]
Example template of recommended content for the schedule of enrolment, interventions, and assessments

### Ethics

Ethics approval for this study was granted on 18 April 2016 by the Ethics Committee of The Sixth Affiliated Hospital of Sun Yat-sen University (reference number 2016ZSLYEC-009). The study protocol, patient information sheets, and informed consent forms were approved by the ethics committee. Informed consent will be obtained from all participants. Participants’ real names will not appear on the relevant reports of this trial in order to protect their privacy.

### Sample size

Our study is designed as a superiority trial whose primary outcome is postoperative reflux gastritis or not. Current experience suggests the predicted rate of postoperative reflux gastritis will be 8% for the uncut Roux-en-Y anastomosis group and 12% for the control group of Billroth II anastomosis. The difference test was used to estimate the sample size with 80% test power and a 5% significance level. Accounting for a 15% drop-out rate and the 1:1 allocation ratio, the total number of patients required per group is 416 (832 in total), which was calculated using the software PASS version 11.0. Considering a completion rate of 75% for each coordinating center, 1040 envelopes were designed for random allocation. The number of cases will be increased if necessary according to the results of the interim analysis.

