### Elimination criteria

Efficacy evaluation of primary outcome: if data for more than three of a total of six time-points (6 months, 1 year, 2 year, 3 year, 4 year, and 5 year) missed for the patient.Did not evaluate the efficacy according to the predetermined plan.

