### Uniformity in surgical performance

Assuring uniformity in surgical performance is the key point for our multi-center clinical trial. Therefore, the surgeons definitely should be trained and the operative procedures monitored. It is worth mentioning that the surgeons should at least have clinical experience in conducting radical gastrectomy for more than 3 years or more than 100 cases.

Before the trial, the leading center will appoint qualified surgeons to train the other surgeons in the coordinating centers. It is relatively easy for them to master the new technique for the reason that the uncut Roux-en-Y anastomosis is based on Billroth II anastomosis with the addition of the side-to-side anastomosis between the jejunum approximately 35 cm from gastrojejunostomy and the jejunum approximately 5 cm from the ligament of Treitz and closure of the intestinal cavity on the input less than 5 cm from the loop gastrojejunostomy anastomosis using uncut closure devices.

In particular, it is required to take pictures of the surgery field including the lymph node dissection area and the anastomosis field in order to make sure that the performance is qualified. These pictures will be uploaded to the database and checked by the data managers. If the operation does not achieve the standard of either D2 gastrectomy or corresponding anastomosis, the case will be rejected.

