All the results of the outcome measures will be recorded at the data center. Only follow-up data of patients without recurrence after 1 year of surgery will be analyzed at the end of the study.

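### The assumption that 85% of randomised patients will be evaluable is not tied to the plan's own post-randomisation removals, nor reconciled with the 75% completion rate in the same paragraph

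*Protocol article*

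**What the plan says.** All references are to the protocol article.

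- **Sample size**, outcome and rates: "Our study is designed as a superiority trial whose primary outcome is postoperative reflux gastritis or not", and "the predicted rate of postoperative reflux gastritis will be 8% for the uncut Roux-en-Y anastomosis group and 12% for the control group" (Billroth II).
- **Sample size**, error rates: "The difference test was used to estimate the sample size with 80% test power and a 5% significance level". Whether the test is one- or two-sided is not stated.
- **Sample size**, attrition: "Accounting for a 15% drop-out rate and the 1:1 allocation ratio, the total number of patients required per group is 416 (832 in total"). Drop-out is not defined.
- **Sample size**, next sentence: "Considering a completion rate of 75% for each coordinating center, 1040 envelopes were designed for random allocation". The section ends by allowing an unspecified increase in numbers after the interim analysis.
- **Elimination criteria**: a patient is removed from the efficacy evaluation of the primary outcome "if data for more than three of a total of six time-points" (6 months and 1, 2, 3, 4 and 5 years) are missed. The Discussion confirms that patients with incomplete efficacy data are excluded.
- **Outcome measures**: "Only follow-up data of patients without recurrence after 1 year of surgery will be analyzed at the end of the study".
- **Uniformity in surgical performance**: "If the operation does not achieve the standard of either D2 gastrectomy or corresponding anastomosis, the case will be rejected". The Randomization section randomises after consent and reveals the arm once the gastrectomy is done, so such a rejection comes after randomisation.

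**The concern.** The power statement depends on the number of patients analysed, and the plan reaches that number from 832 with a single undefined percentage. Three other sections take randomised patients out of the analysis for reasons that go beyond ordinary loss to follow-up. The population has stage I–III gastric cancer and is followed for 5 years, and survival and recurrence are themselves planned outcomes, so some loss by these routes must be expected. Nothing in the Sample size section shows that it was counted.

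The same paragraph also contains a second attrition figure, 75%, which does not match 85%. It may describe recruitment by centre rather than completion by patients, but the text does not say.

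At stake is whether the evaluable number can be relied on. If the base sample size were recalculated and the 15% carried over unexamined, the new figure could again miss its stated power.

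**Working it through.** **1. The plan's own figure.** Inputs from Sample size: p₁ = 0.08, p₂ = 0.12, difference 0.04, power 80%, significance level 5%, drop-out 15%. With the pooled two-proportion formula:

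n = [z_α·√(2p̄(1−p̄)) + z_β·√(p₁(1−p₁)+p₂(1−p₂))]² / 0.04²

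Here p̄ = 0.10, the first root is 0.4243 and the second 0.4233.

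- Two-sided: (1.960 × 0.4243 + 0.8416 × 0.4233)² / 0.0016 gives 882 evaluable per group; 882 / 0.85 = 1038 randomised per group.
- One-sided: 695 evaluable, 818 randomised per group.

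Neither gives 416. Continuity-corrected, unpooled and arcsine versions do not either (randomised per group, two-sided / one-sided: 1097 / 876, 1036 / 816, 1030 / 811). The stated figure is therefore not reproduced, and that is a larger fault than the one treated here.

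**2. What the 15% allows.** 416 × 0.85 = 353.6, about 354 evaluable. That leaves about 62 losses per group from all causes.

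**3. How the removal rules act.**

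- *Missed time-points.* Someone who dies before the 2-year visit can supply at most the 6-month and 1-year assessments, so four of six are absent. The rule removes that patient if visits after death count as missed. The text does not say whether they do.
- *Recurrence.* The wording can mean recurrence-free at 1 year, or no recurrence at any time after the first year. The two imply different losses.
- *Rejected operations.* These occur after randomisation. No rate is given.

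**4. How much room is left (assumed rates).** If ordinary loss takes L and the other removals take a fraction f of the remainder, 85% evaluable requires (1−L)(1−f) ≥ 0.85.

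- L = 5%: f ≤ 1 − 0.85/0.95 = 10.5%.
- L = 10%: f ≤ 1 − 0.85/0.90 = 5.6%.

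For scale, with exponential survival and 5-year survival S₅, the proportion dead before 2 years is 1 − S₅^(2/5). This gives 8.5% for S₅ = 80%, 13.3% for 70% and 18.5% for 60%. L and S₅ are assumptions; the article gives neither.

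**5. The 75% figure.** 1040 × 0.75 = 780, not 832. 832 / 0.75 = 1109, not 1040. The envelopes equal 832 × 1.25, which corresponds to 832/1040 = 80% completion. So 75% agrees neither with the 85% nor with its own use.

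**6. Power over a range of evaluable fractions, 832 randomised.** Power = Φ{[0.04·√n − z_α × 0.4243] / 0.4233}. For n = 354, two-sided: (0.7526 − 0.8315) / 0.4233 = −0.186, and Φ = 42.6%.

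| Evaluable | n per group | Two-sided power | One-sided power | Randomised per group for 882 evaluable |
|---|---|---|---|---|
| 85% | 354 | 42.6% | 55.1% | 1038 |
| 75% | 312 | 38.4% | 50.8% | 1176 |
| 65% | 270 | 34.1% | 46.2% | 1357 |

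**7. If only the formula were corrected.** With 1038 per group and 75% evaluable, n = 778.5. Then (0.04 × √778.5 − 0.8315) / 0.4233 = 0.672, so power is 74.9% instead of 80%.

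**The case against.** The strongest reply is that the article never defines drop-out and gives no rate for death, recurrence or rejected operations. The 15% may have been meant as an all-cause allowance. Several points support caution:

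- The elimination rule is lenient. A patient who attends at 6, 12 and 24 months and is then lost misses exactly three time-points and stays in, so late loss to follow-up need not cost an evaluable patient.
- The removals may overlap. A patient with recurrence who dies early is lost once, not twice.
- With assumed 5-year survival of 80% or 70%, deaths before 2 years (8.5%, 13.3%) lie within 15%; only the 60% assumption exceeds it.
- The paragraph provides 1040 envelopes and a possible increase after the interim analysis. If all 1040 were used and 75% completed, 390 per group would remain, with two-sided power of 46.1%.
- An article often leaves a breakdown of attrition to the full protocol.

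These points defeat a stronger claim that a reader might infer: that the 15% is demonstrably too small and 85% evaluable cannot be reached. The documents do not support that. They do not defeat the narrower point. The 15%, the 75% and all three removal rules are stated in this article, so their lack of connection is not a matter of missing detail. The planned recruitment is 832, not 1040, and the interim increase has no stated size or rule.

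**Conclusion.** The 85% evaluable fraction is undefined, unsupported against the plan's own removals, and unreconciled with the 75% completion rate. The total loss could be below or above 15%. That it plausibly exceeds 15% is a judgement about stage I–III gastric cancer over 5 years under the assumed rates shown, not something the article establishes.

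The size is moderate: going from 85% to 75% evaluable costs about 4 points of two-sided power, and going to 65% costs about 8.5. These figures assume 8% versus 12% and the pooled test; one-sided power is higher but falls in the same way. The effect is secondary to the base-size fault, which alone puts two-sided power at 42.6% against the stated 80%. It still deserves its own correction, because repairing the formula would not repair this input.

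**What to change.** **Sample size section.** Define what the 15% covers. State assumed rates, with a range, for loss to follow-up, death, recurrence and rejected operations, and how far they overlap. Say what the 75% completion rate measures, and reconcile it with the 15% and with the 1040 envelopes. Restate the evaluable number per group and the power at 832 over that range, and name the sidedness of the test.

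**Elimination criteria, Uniformity in surgical performance, and Outcome measures.** Keep in the primary analysis every randomised patient with at least one postoperative endoscopy, including those with later recurrence or death and those whose operation was judged below standard. Table 1 schedules endoscopy at 6 and 12 months, so patients who are lost, recur or die after the 6-month examination would still contribute, which reduces the loss. State how death and recurrence are handled in that analysis, and align the Discussion's sentence on incomplete efficacy data.

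**Cost.** A recalculated paragraph, three amended rules and a less favourable stated power. No extra patients are required to make these changes; restoring 80% power is a separate decision that belongs with the correction of the base sample size.

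### 832 patients do not give 80% power for 8% versus 12% reflux gastritis; the two-sided power is about 43%

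*Protocol article*

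**What the plan says.** The Sample size section of the protocol article sets out the whole calculation:

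- Outcome and hypothesis: "Our study is designed as a superiority trial whose primary outcome is postoperative reflux gastritis or not".
- Rates: "the predicted rate of postoperative reflux gastritis will be 8% for the uncut Roux-en-Y anastomosis group and 12% for the control group" undergoing Billroth II.
- Error rates: "The difference test was used to estimate the sample size with 80% test power and a 5% significance level". Neither this section nor Statistical analysis says whether the test is one- or two-sided.
- Drop-out of 15% and 1:1 allocation.
- Result: "the total number of patients required per group is 416 (832 in total), which was calculated using the software PASS version 11.0".
- Envelopes: "Considering a completion rate of 75% for each coordinating center, 1040 envelopes were designed for random allocation".

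The abstract repeats the target: "We will recruit 832 patients who meet the trial eligibility criteria". The Statistical analysis section names Pearson's chi-square or Fisher's exact test for categorical variables. The Sample size section closes by allowing the number to be raised after the interim analysis, without giving a rule.

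**The concern.** A four-point difference between rates near 10% is small, and 416 per group before drop-out is far too few to detect it with 80% power. All the inputs are in one paragraph, so the result can be checked without any outside figure.

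This is the main design claim of a phase III superiority trial. If the true power is about half the stated power, a real difference of the planned size would probably be missed under a two-sided test. A non-significant result would then be read as evidence from an 80%-powered trial.

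**Working it through.** **Inputs** (all from Sample size): p1 = 0.08, p2 = 0.12, difference 0.04, mean rate 0.10, power 80% (z = 0.8416), alpha 5% (z = 1.9600 two-sided, 1.6449 one-sided), drop-out 15%, 1:1 allocation.

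**Attempt to reproduce 416 per group.** Pooled two-proportion formula, per group:

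n = [z_alpha × √(2 × 0.10 × 0.90) + z_power × √(0.08 × 0.92 + 0.12 × 0.88)]² / 0.04²

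The two square roots are √0.18 = 0.42426 and √0.1792 = 0.42332.

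- Two-sided: (1.9600 × 0.42426 + 0.8416 × 0.42332)² / 0.0016 = 881.8, so 882 evaluable; 882 / 0.85 gives 1,038 randomised per group, 2,076 in total.
- One-sided: (1.6449 × 0.42426 + 0.8416 × 0.42332)² / 0.0016 = 694.5, so 695 evaluable; 695 / 0.85 gives 818 per group, 1,636 in total.

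Other versions, per group after dividing by 0.85:

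| Version | Two-sided | One-sided |
|---|---|---|
| Pooled | 1,038 | 818 |
| Pooled with continuity correction | 1,097 | 876 |
| Unpooled | 1,036 | 816 |
| Arcsine | 1,030 | 811 |

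Multiplying by 1.15 instead of dividing by 0.85 gives 1,007 to 1,072 two-sided and 793 to 856 one-sided. None of these is near 416, so the stated figure is not reproduced.

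**Power of the stated design.** Evaluable per group: 416 × 0.85 = 353.6, about 354.

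power = Φ[(0.04 × √n − z_alpha × 0.42426) / 0.42332]

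- n = 354, two-sided: Φ[(0.7526 − 0.8315) / 0.42332] = Φ(−0.186) = 42.6%. Exact enumeration of the Pearson chi-square test gives 42.8%.
- n = 354, one-sided: Φ[(0.7526 − 0.6979) / 0.42332] = Φ(0.129) = 55.1%.
- n = 416, no drop-out: 48.5% two-sided, 61.0% one-sided.

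**What 354 per group can detect.** Holding the Billroth II rate at 12% and solving for 80% power gives an uncut Roux-en-Y rate of about 6.0% two-sided (about 6.6% one-sided). As a cross-check, 6% versus 12% two-sided needs 355.9, so 356 evaluable, and 356 / 0.85 gives 419 per group, close to 416.

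**Envelopes.** 1040 × 0.75 = 780, which is 832 − 780 = 52 below target. 832 / 0.75 = 1,109.3, so 1,110. The printed 1040 equals 832 / 0.80, which is also 832 × 1.25.

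**The case against.** **Sidedness.** Since it is not named, the one-sided reading deserves a hearing. At 55% one-sided power the trial would be slightly more likely to find the planned effect than to miss it, so the statement that it would probably miss depends on a two-sided test. That qualification is fair. However, the named Pearson chi-square test is non-directional, so two-sided is the natural reading, and neither reading comes near 80%.

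**Interim increase.** The Sample size section allows more cases after the interim analysis. No rule is given there or under Interim analysis, which describes the look at 400 cases as a search for superiority. An unspecified later increase cannot make true the claim that 416 per group is what 80% power requires.

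**Possible origins.** Three near matches exist: 6% versus 12% (419 per group); the one-sided per-group figure of 818 taken as a total; and a one-sample, one-sided test against a fixed 12% (364 × 1.15, about 419). All are conjecture. The first uses a rate the protocol does not state, the second would itself be a mistake, and the third is not a two-group comparison.

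**Back-fitting.** Adopting 6% as the planning rate because it suits 832 would fit the assumption to the sample; the protocol predicts 8%. This stands: 6% may be reported only as the detectable rate.

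**Envelopes.** The completion rate is not defined. If it means patients completing follow-up, 780 exceeds the 832 × 0.85 = 707 evaluable patients implied by the drop-out allowance, and there is no shortfall. The plain reading still gives 1,110, but this point is secondary and calls first for a definition.

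**Conclusion.** The concern holds. The stated sample size is wrong for the stated assumptions under every standard two-group version tried. Two-sided at 5%, 832 randomised gives 42.6% power for 8% versus 12% after 15% drop-out. The required number would be 2,076, about two and a half times as many (2,076 / 832 = 2.50). On the most favourable reading, one-sided with nobody lost, power is about 61%.

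These figures rest on the protocol's own rates and on 15% being the full loss. The article also rejects cases with inadequate surgery, eliminates patients who miss too many time-points, and limits the final analysis by recurrence. If these together remove more than 15%, power is lower still.

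The envelope count disagrees with its stated rate on the plain reading, by 52 patients. The main finding does not depend on it.

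**What to change.** Correct the Sample size statement:

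- Name the sidedness of the 5% level.
- State that 832 randomised, about 354 evaluable per group, gives about 43% power for 8% versus 12% at two-sided 5%.
- If useful, add that 80% power against a 12% control rate is reached only if the uncut Roux-en-Y rate is about 6%. Label this as the detectable effect, not as a new planning assumption.
- Remove the claim that 416 per group is what 80% power requires under the stated rates.
- Define the completion rate. Then either prepare at least 1,110 envelopes or, if 80% was meant, say so.

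The cost is protocol wording, a less favourable stated power and about 70 more envelopes (1,110 − 1,040). No extra patients are needed. If the sponsor prefers to keep 80% power for 8% versus 12%, the target becomes 2,076 two-sided.

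### The stated 832 patients give about 43% power (two-sided 5%) for 8% versus 12%, not the stated 80%

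*Protocol article*

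**What the plan says.** The Sample size section of the protocol article defines the design target: "Our study is designed as a superiority trial whose primary outcome is postoperative reflux gastritis or not". It gives the planning rates, "the predicted rate of postoperative reflux gastritis will be 8% for the uncut Roux-en-Y anastomosis group and 12% for the control group", and the error rates: "The difference test was used to estimate the sample size with 80% test power and a 5% significance level". After a 15% drop-out allowance and 1:1 allocation, the result is "the total number of patients required per group is 416 (832 in total), which was calculated using the software PASS version 11.0". The abstract repeats the total: "We will recruit 832 patients who meet the trial eligibility criteria".

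The section does not say whether the 5% is one-sided or two-sided. The Statistical analysis section also gives only a 5% level, and plans Pearson's chi-square or Fisher's exact test for categorical outcomes. The Sample size section adds that 1,040 randomization envelopes were prepared and that enrolment may be raised after the interim analysis. It gives no rule for that increase.

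**The concern.** A four-point difference between proportions near 10% usually needs far more than 350 evaluable patients per group for 80% power, so 416 enrolled per group looks too small on sight. The section gives every input and the result, so it can be checked without any other document.

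The power claim is the justification for 832 patients, and it governs how the primary result is read. Readers who believe the trial had 80% power for a four-point reduction would take a non-significant result as fairly strong evidence against such a reduction. If the real power is near 43%, that reading is wrong.

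**Working it through.** **Inputs** (all from Sample size): p1 = 0.08, p2 = 0.12, difference 0.04, power 80%, level 5%, 1:1 allocation, drop-out 15%. Sidedness is not stated, so both cases are computed. Normal quantiles: 1.960 (two-sided 5%), 1.645 (one-sided 5%), 0.842 (80% power).

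**Step 1. Try to reproduce 416.**

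Unpooled variance: n = (z_alpha + z_beta)² × [p1(1−p1) + p2(1−p2)] / (p2−p1)², where p1(1−p1) + p2(1−p2) = 0.0736 + 0.1056 = 0.1792.

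Pooled variance: n = [z_alpha × √(2 × 0.10 × 0.90) + z_beta × √0.1792]² / 0.04².

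Evaluable numbers are rounded up, divided by 0.85 and rounded up again:

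| Per group | Evaluable, two-sided | Enrolled, two-sided | Evaluable, one-sided | Enrolled, one-sided |
|---|---|---|---|---|
| Unpooled | 880 (879.1) | 1,036 | 693 (692.4) | 816 |
| Pooled | 882 (881.8) | 1,038 | 695 (694.5) | 818 |
| Arcsine | 875 | 1,030 | 689 | 811 |
| Continuity-corrected | 932 | 1,097 | 744 | 876 |

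Inflating for drop-out by multiplying by 1.15 does not help: the smallest result is then 793 per group. No variant comes near 416.

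For the unpooled and pooled formulas the totals are 2,072 to 2,076 two-sided and 1,632 to 1,636 one-sided. The planned 832 is 832/2,076 = 40% of the two-sided requirement and 832/1,636 = 51% of the one-sided one.

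**Step 2. Power that the planned number gives.** Evaluable per group: 416 × 0.85 = 353.6, taken as 354.

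Power = Φ{[0.04 − z_alpha × √(0.18/n)] / √(0.1792/n)}.

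For n = 354, two-sided: (0.04 − 1.960 × 0.02255) / 0.02250 = −0.186, so power is 42.6%.

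| Evaluable per group | Two-sided 5% | One-sided 5% |
|---|---|---|
| 354 (15% drop-out) | 42.6% | 55.1% |
| 416 (no drop-out) | 48.5% | 61.0% |
| 520 (all 1,040 envelopes used, no drop-out) | 57.6% | 69.4% |

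Exact binomial enumeration of the chi-square test agrees: 42.8% (354 per group) and 48.8% (416 per group) two-sided.

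**Step 3. What if the trial observed exactly its planned rates?** With 354 per group, z = 0.04 / √(0.18/354) = 1.774, two-sided p = 0.076. The 95% confidence interval half-width is 1.96 × √(0.1792/354) = 4.41 points, so the interval for the reduction runs from −0.4 to 8.4 points. The planned effect itself would not reach two-sided significance.

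**Step 4. What the planned number can detect.** With about 354 evaluable per group and a control rate of 12%, 80% two-sided power needs an experimental rate of about 6%. With the experimental rate held at 8%, it needs a control rate of about 14.8%.

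**Step 5. Possible origins (conjecture).**
- 6% versus 12%, unpooled and two-sided: (1.960 + 0.842)² × (0.0564 + 0.1056) / 0.06² = 353.2, and 353.2/0.85 = 415.5, which rounds up to 416. Rounding to 354 before the division gives 417, and the pooled formula gives 419.
- The one-sided requirement of 811 to 818 per group is within 3% of 832, so a per-group figure may have been taken as the total.
- A one-sample, one-sided formula needs 364 evaluable, or 419 to 428 with drop-out. It does not apply to a two-arm comparison.

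The article does not settle which of these, if any, is right.

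**The case against.** The strongest objection is that the protocol never says the test is two-sided. On a one-sided 5% test the power is 55%, and it would then be untrue that the trial is more likely to miss the effect than to find it. This stands as a limit on that one statement. The planned chi-square or Fisher test makes two-sided the natural reading, but that is an inference. It does not rescue the claim, because 55% is also far below 80%.

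A second objection is that the protocol allows enrolment to rise after the interim analysis, so 832 may not be final. The provision exists, but it has no target or rule, and the Interim analysis section describes a search for clear superiority, not a re-estimation of sample size. It does not make 416 per group deliver 80% power.

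A third is that nothing in the article mentions 6%, and the match to 416 depends on the formula and on the order of rounding. This is correct. The inputs and the result are inconsistent as a set, and the article alone does not show which is wrong: a rate, the power, the sidedness, or a confusion of per-group and total numbers. The inconsistency does not depend on the explanation.

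The article is a condensed account, but that does not excuse the point: the calculation is given in full and its result does not follow.

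**Conclusion.** The concern holds. For 8% versus 12%, 416 enrolled per group with 15% drop-out gives about 43% power at a two-sided 5% level and about 55% at a one-sided level, against a stated 80%. The claim fails with any standard two-proportion formula, with either sidedness, with no drop-out, and even if all 1,040 envelopes produced complete data. On the two-sided reading the trial would miss its own planned effect about 57% of the time.

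These figures assume that exactly 85% of patients are evaluable. The Elimination criteria and the restriction of the final analysis to patients without recurrence (Outcome measures) would lower power further if the 15% does not already cover them. The paragraph must be corrected, because it misstates what a non-significant primary result would mean.

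**What to change.** Retrieve the PASS output, identify which input or result was misreported, and correct the Sample size section accordingly. State whether the 5% is one-sided or two-sided.

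- If 8% versus 12% stands with 832 patients, say that about 354 evaluable per group gives about 43% power two-sided (55% if the test is one-sided), and that the effect detectable with 80% two-sided power is about 6% versus 12%.
- If the output shows that 6% was the rate used, replace the 8%. Do not change the rate merely to fit 416.
- In either case, state that a non-significant primary result does not exclude a four-point benefit, and report the difference in proportions with its 95% confidence interval (expected half-width about 4.4 points at 8% versus 12%).

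The cost is a rewritten paragraph and, if 8% versus 12% stands, a less favourable power statement. No extra patients are needed for this correction. Keeping both 80% power and 8% versus 12% would instead need about 2,072 to 2,076 patients two-sided, or 1,632 to 1,636 one-sided.
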